**Intervention groups**																		
		CM^b^	N/A^c^		N/A		✓^d^		✓		✓		✓		N/A			
		CL^e^	N/A		N/A		✓		✓		✓		✓		N/A			
**Primary outcome**																		
		DERS-SF^f^	18		✓		✓		✓		✓		✓		✓			
**Secondary outcomes**																		
		Depression (PROMIS^g^)	4		✓		✓		✓		✓		✓		✓			
		Anxiety (PROMIS)	4		✓		✓		✓		✓		✓		✓			
		QoL^h^ (PROMIS)	30		✓		N/A		N/A		N/A		✓		✓			
**Module-specific target outcomes**																		
		BES^i^	12		✓		✓		✓		✓		✓		✓			
		SMQ^j^	16		✓		✓		✓		✓		✓		✓			
		CERQ^k^	8		✓		✓		✓		✓		✓		✓			
		UP-CSQ^l^	7		✓		✓		✓		✓		✓		✓			
		MEAQ-30^m^	30		✓		✓		✓		✓		✓		✓			
**Other measures**																		
		Depression Risk Questionnaire-7	7		✓		N/A		N/A		N/A		N/A		N/A			
		Positive Affect Subscale	10		✓		N/A		N/A		N/A		✓		✓			
		Demographic and cancer information	39		✓		N/A		N/A		N/A		N/A		N/A			
		Health service use (eg, current medications, mental health treatment)	10		✓		N/A		N/A		N/A		✓		✓			
		Program evaluation (Client Satisfaction Questionnaire and open feedback)	10		N/A		N/A		N/A		N/A		✓		N/A			
		Credibility Expectancy Questionnaire	6		✓		N/A		N/A		N/A		N/A		N/A			
		Adverse events (assessed throughout)	N/A		N/A		✓		✓		✓		✓		✓			
		COVID-19 pandemic impact and distress	2		✓		N/A		N/A		N/A		✓		N/A			
		MINI^n^	5 mins		✓		N/A		N/A		N/A		N/A		N/A			

^a^Completion times: T0, T4, and T5 were 25 minutes each; T1-T3 were 10 minutes each.

^b^CM: CanCope Mind.

^c^N/A: not applicable.

^d^Measure administered at that time point.

^e^CL: CanCope Lifestyle.

^f^DERS-SF: Difficulties With Emotion Regulation Scale–Short Form.

^g^PROMIS: Patient-Reported Outcomes Measurement Information System. The PROMIS scales are all computer-adaptive tests, which means that they vary in the number of items administered depending on the participants’ prior responses.

^h^QoL: quality of life.

^i^BES: Beliefs About Emotions Scale.

^j^SMQ: Southampton Mindfulness Questionnaire.

^k^CERQ: Cognitive Emotional Regulation Questionnaire. “Catastrophizing” and “Refocus on Planning” subscales.

^l^UP-CSQ: Unified Protocol–Cognitive Skills Questionnaire.

^m^MEAQ-30: Multidimensional Experiential Avoidance Questionnaire-30.

^n^MINI: Mini International Neuropsychiatric Interview.

#### Screening

The MINI [45] is conducted in an initial phone call and used as a diagnostic tool to assess the presence of a major depressive episode (module A) and generalized anxiety disorder (module N), ruling out organic causes (module O). MINI interviews are recorded, allowing for the assessment of reliability and team discussion of complex cases. Any participant who endorses the criteria for a psychiatric illness is provided with relevant mental health and emergency support numbers.

#### Primary Outcome

The Difficulties in Emotion Regulation Scale–Short Form (DERS-SF) [47] will be used to assess six domains of emotional regulation (ie, acceptance of emotional responses, emotional awareness, emotional clarity, engagement in goal-directed behaviors, impulse control, and access to emotion regulation strategies). The DERS-SF is an 18-item self-report questionnaire that asks participants to indicate the frequency of emotion-focused behaviors and thoughts on a Likert-type rating scale, with possible responses ranging from 1 (“Almost never”) to 5 (“Almost always”). Example items include “I have difficulty making sense of my feelings” and “When I’m upset, I become out of control.” Scores can range from 18 to 90, with higher scores indicating greater emotional dysregulation. The DERS-SF indicates good concurrent validity for depression, anxiety, and self-harm measures and demonstrates good internal consistency reliability for both the overall scale (Cronbach α=.90) and each individual subscale (Cronbach α ranging from .78 to .89) [48,49]. Moreover, the full version of the Difficulties in Emotion Regulation Scale has been used in prior research to assess emotion dysregulation in oncology populations [50].

#### Secondary Outcomes

The PROMIS–computer [51,52] adaptive tests for the Anxiety and Depression scales will be used to measure symptom changes. The computer-adaptive test algorithm requires a minimum of 4 items and a maximum of 12, and the test stops when the SE is less than 0.30 [51]. The scales present the statement “over the past 7 days...” followed by items, such as “I felt uneasy” (PROMIS Anxiety) and “I felt helpless” (PROMIS Depression). Each item response is rated on a 5-point Likert-type frequency scale, ranging from 1 (“Never”) to 5 (“Always”). Raw scores for each item are summed and converted into a *T* score (population mean 50, SD 10). Higher scores indicate greater depressive or anxiety symptoms (*T*<65 = normal-to-mild; *T*≥65 = moderate to severe symptoms [53]).

The PROMIS QoL Health Utility Score [54] will be calculated using preference-based weights in PROMIS−29+2 Profile (version 2.1) [55] based on computer-adaptive testing to assess QoL. The QoL outcome score is a composite of the following seven domains captured by PROMIS: physical function, pain interference, cognitive function, depression, fatigue, sleep disturbance, and the ability to participate in social roles and activities. The QoL score ranges from −0.022 (“Dead”) to 1.0 (“Full health”) and has achieved good construct validity when measured against the Health Utility Index and the EQ-5D [56].

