#### Randomization and Blinding

Randomization to CM or CL is conducted using a stratified, block randomization scheme generated in advance and uploaded to REDCap. Variable block sizes (4, 6, or 8) are used to ensure allocation concealment and prior guessing of the allocation sequence at the end of each block. Randomization is stratified by baseline depressive and anxiety symptoms as measured by the Patient-Reported Outcomes Measurement Information System (PROMIS) Anxiety and Depression scales (2 strata: ≥60 for either depression or anxiety, <60 for both depression and anxiety) and the Difficulties in Emotion Regulation Scale–Short Form (2 strata: <45 and ≥45). The randomization scheme is generated and set up in REDCap by a member of the research staff who is not involved in the recruitment or delivery of the intervention nor in the subsequent statistical analysis. The participants are aware of their intervention allocation (ie, CM or CL); thus, they are not blinded. However, participants remain unaware of the study hypotheses regarding which group will improve more on outcomes, and both treatments are presented as potentially effective.

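### The stated scoring rule for PROMIS Anxiety and Depression (summed raw items converted to T) does not fit the adaptive tests of varying length that the same paragraph describes.

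*Protocol article*

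**What the plan says.** Under Assessment Time Points and Measures, Secondary Outcomes, the protocol article says that PROMIS computer-adaptive versions of the two symptom scales are used. The algorithm "requires a minimum of 4 items and a maximum of 12, and the test stops when the SE is less than 0.30". Footnote g to Table 3 says of the PROMIS scales that "they vary in the number of items administered depending on the participants’ prior responses". Items are scored 1 to 5.

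The same Secondary Outcomes paragraph then gives the scoring rule: "Raw scores for each item are summed and converted into a" T score with population mean 50 and SD 10. No section describes item-response-theory scoring, or a conversion that depends on which items, or how many, were given.

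The T scores are used in four places:
- Anxiety and depression are two of the three secondary outcomes (Primary Aim).
- They are the outcomes of the mediation analysis (Aim 3).
- They define one of the two stratification factors (Randomization and Blinding): "2 strata: ≥60 for either depression or anxiety, <60 for both depression and anxiety".
- A worsening of more than 10 T points is one of three adverse-event tracking routes (Ethics Approval and Adverse Events).

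**The concern.** A single table from raw sum to T presumes that everyone answered the same items. In an adaptive test, people answer different items and different numbers of them, so the sum mixes severity with test length. The mixing is also directional. Items about distress carry little information on people with few symptoms, so the standard error falls more slowly for them and they tend to receive more items, each adding at least 1 point.

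If the rule were followed literally, a participant who improves toward the floor could be given a longer test and show a sum that is unchanged or higher. That would blur the group contrasts on anxiety and depression, weaken the mediation analysis, misplace people around the cut at 60 and make the 10-point flag unreliable.

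This is not a detail left to an unseen document. The article states a scoring rule, and the rule conflicts with the instrument it describes.

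**Working it through.** The plan gives no figure to reproduce on this point. The check has two parts.

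**1. Arithmetic with the article's own inputs** (4 to 12 items, each scored 1 to 5)

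- Range of the sum with 4 items: 4 × 1 = 4 to 4 × 5 = 20.
- Range of the sum with 12 items: 12 × 1 = 12 to 12 × 5 = 60.
- Twelve answers of 1 (no symptoms): 12 × 1 = 12. Four answers of 3 (mid-scale): 4 × 3 = 12. The sums are equal.
- Four answers of 2, 3, 3, 3: 2 + 3 + 3 + 3 = 11, which is below the symptom-free respondent's 12.

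A single increasing conversion preserves the order of the sums, so it cannot repair this.

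**2. Illustrative simulation of the stated stopping rule**

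The article gives no item parameters, so these are assumptions: a graded response model, a 28-item bank with five categories, items chosen for maximum information, at least 4 and at most 12 items, and a stop at posterior SE below 0.30 on the standardized latent scale. Each setting had 4,000 simulated people with true T of mean 55 and SD 10. Four slope ranges were crossed with two bank locations. Low distress means true T below 45; moderate means 55 to below 65. Mis-ordered means that the low-distress person has the strictly higher score.

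| Slopes | Location | Mean items, low / moderate | Median sum, low / moderate | Pairs mis-ordered by sum | Rank correlation with true T, sum / model-based |
|---|---|---|---|---|---|
| 1.5–2.5 | 0.3 | 9.38 / 6.73 | 14 / 22 | 1.4% | 0.856 / 0.953 |
| 1.5–2.5 | 0.8 | 11.08 / 7.21 | 14 / 20 | 5.2% | 0.800 / 0.955 |
| 2–3 | 0.3 | 7.31 / 5.09 | 11 / 16 | 5.4% | 0.797 / 0.955 |
| 2–3 | 0.8 | 10.13 / 5.00 | 13 / 14 | 30.4% | 0.609 / 0.955 |
| 2.5–3.5 | 0.3 | 6.92 / 4.18 | 8 / 13 | 12.5% | 0.790 / 0.957 |
| 2.5–3.5 | 0.8 | 8.97 / 4.20 | 11 / 10 | 46.2% | 0.510 / 0.958 |
| 3–4 | 0.3 | 5.83 / 4.03 | 7 / 13 | 4.2% | 0.882 / 0.962 |
| 3–4 | 0.8 | 7.83 / 4.01 | 9 / 11 | 20.0% | 0.772 / 0.963 |

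Model-based scoring of the same responses mis-ordered 0.0% of pairs in every setting. In all eight, the low-distress group received more items and the sum tracked severity less well than the model-based score. The size of the loss varies widely with the assumed bank.

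**The case against.** The strongest reply is that this is loose wording and not a scoring plan. A test that stops when its SE is small enough must keep a running model-based estimate for each participant, so a correct score exists whenever the algorithm runs. The article describes no table for sums of 4 to 12 items, and the randomization and adverse-event rules are on the T metric, not on raw sums. Mis-ordering also would not follow if the conversion were specific to the items each person received. All of this stands. It makes the consequence conditional, but it does not remove the contradiction: no section corrects the sentence, and an analyst following the published text would compute the wrong score.

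One might also argue that Table 3, which lists 4 items for each scale, points to a fixed four-item form for which a sum would be legitimate. Footnote g to that table rules this reading out.

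A reader might infer that participants in this trial were in fact mis-scored, or that summing generally places low-distress people above moderately distressed ones. The documents support neither. They do not show which score was exported. The reversal of group medians appears in only one of the eight assumed settings (11 against 10), and in the mildest setting 1.4% of pairs are mis-ordered.

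Nor does the point reach the validity of the tests. Under the planned permutation inference, a poorly scored outcome need not inflate the type I error; the harm is to the estimates, their interpretation and power.

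**Conclusion.** The description of PROMIS scoring is internally inconsistent and should be corrected. That conclusion rests on the text alone.

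The consequence holds only if the sentence was applied as written with one common conversion. In that case the score depends on test length, with 1% to 46% of low/moderate pairs mis-ordered and rank correlations of 0.51 to 0.88, against 0.0% and 0.95 to 0.96 for model-based scoring. These figures rest on assumed item parameters and show direction and range, not an estimate for this trial.

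The reach is two secondary outcomes, the mediation outcomes, one stratification factor and one adverse-event flag. The primary outcome, DERS-SF, is a fixed 18-item scale whose scoring is untouched. The anxiety/depression stratum does enter its model as a covariate, which is a reason to leave the recorded strata as they are.

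**What to change.** Replace the scoring sentence with: *The T score is the model-based (item response theory) score returned by the adaptive-test engine; raw item scores are not summed.* In Table 3, mark the 4 items shown for each scale as the minimum. Confirm which score field was exported and used.

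If raw sums turn out to have been used, re-score the baseline and outcome T scores and the adverse-event flag from the stored item responses before analysis.

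Do not replace the strata. All 224 participants are randomized and follow-up is complete, and the planned randomization-based inference must reflect the allocation as it was made. Keep the strata actually used for both the covariates and the permutation scheme, and use a re-scored stratum only in a sensitivity analysis.

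The cost is one sentence, one table note and one check of the export. No new data are needed; re-scoring, if required, depends on the item responses having been stored.

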#### Module-Specific Target Outcomes

All the module-specific target outcomes and their respective modules are listed in Table 1. The Beliefs About Emotions Scale [39] will be used to assess negative beliefs about emotions and the impact of CM’s module 1. The Southampton Mindfulness Questionnaire [40] will be used to assess mindfulness and the impact of CM’s module 2. The Unified Protocol–Cognitive Skills Questionnaire [32] will be used to assess cognitive reappraisal skills and the impact of CM’s module 3. In addition, the Cognitive Emotional Regulation Questionnaire [41] “Catastrophizing” and “Refocus on Planning” subscales will also be used to assess the impact of CM’s module 3. The Multidimensional Experiential Avoidance Questionnaire-30 [42] will be used to assess levels of emotional (experiential) avoidance and to assess the impact of CM’s module 4.

#### Intervention Evaluation Outcomes

The Credibility Expectancy Questionnaire [57] will be administered to assess the perceived credibility and expectancy of CM versus CL before commencing the intervention. The Client Satisfaction Questionnaire [58] will be used to assess the participants’ level of satisfaction with CM and CL. Questions will assess factors such as whether the intervention has met participants’ needs and whether participants would return to the service. Higher scores indicate greater satisfaction. With regard to evaluation of treatment fidelity and reliability, because both interventions are delivered in a standardized way via the internet, no additional measures of treatment fidelity or reliability are collected. With regard to adherence, for CM, adherence is measured objectively via the number of completed application activities on the web per module. For CL, adherence is measured via self-reports of whether participants indicate that they have applied the intervention content to their lives that week in the weekly web-based activities.

#### Other Measures

The Depression Risk Questionnaire-7 [59] is a brief self-reported questionnaire developed as a clinical screening tool for patients with breast cancer at risk of depression. The Positive Affect Subscale from the Positive and Negative Affect Scales [60] will be used to assess positive emotional states (eg, attentiveness, enthusiasm, pride, and interest). Two items assessing (1) impact and (2) distress caused by COVID-19 will be administered, with participants’ self-reported responses indicated on a sliding scale from 0 to 100 (0=no distress or no impact, 100=a lot of distress or a lot of impact).

### Participant Compensation

All eligible participants who complete the baseline assessment as well as at least 2 modules and their respective postintervention assessments (ie, half of an intervention, T_1_ and T_2_) are provided with an e-gift card worth equivalent to Aus $40 (US $30) in their local currency as a token of appreciation. This compensation is provided at the end of their participation.

### Statistical Analysis Plan

#### Power Analysis

The primary end point for the trial is the immediate postintervention assessment (T_4_). As all primary and secondary outcomes are continuous, the primary analyses will be linear regressions with group as a predictor and outcome scores at baseline included as a covariate. We set the type 1 error at Cronbach α=.05 (2-tailed). A Monte Carlo simulation study was conducted to determine the power analysis and required sample size. In the simulation, we varied (1) the correlation between baseline and postintervention outcome scores (*r*) across four values (0.3, 0.4, 0.5, and 0.6) selected from the literature and our pilot research [18] and (2) the standardized mean difference (SMD) between the CM and CL groups at post intervention on outcome scores (primary end point) across 2 values (SMDs of 0.5 and 0.6). The SMDs were selected based on our pilot work [18] where we observed SMDs from before to after the intervention of approximately 0.5 to 1.0 for our primary and secondary outcomes. Our pilot did not include a control group (likely inflating the SMDs) but only tested individual modules separately (likely reducing the SMDs); therefore, we believe that a moderate SMD was reasonable, on average. The code for this Monte Carlo study is publicly available [61]. Results from 10,000 Monte Carlo simulations for each of the conditions and varying sample sizes showed that participants (n=100) with complete data at T_4_ will provide more than 80% power to detect a medium (SMD=0.5) group difference—after the intervention, even with only a moderate correlation (*r*=0.3) between baseline and postintervention outcome scores with Cronbach α=.05.

#### Primary Aim

Missing data are ubiquitous in research, and dropout and incomplete data (eg, dropout) are particularly common in web-only trials [62]. For aim 1 analyses, we will address missing data using multiple imputation with a fully conditional specification [63] and predictive mean matching [64]. A total of 20 imputed data sets will be generated. The primary outcome of the trial is the Difficulties in Emotion Regulation Scale (DERS-SF). The primary end point is immediately after the intervention, immediately following module 4 (T_4_). Anxiety and depression symptoms as well as overall QoL are secondary outcomes. All outcomes are continuous measures.

The primary analyses will consist of linear regressions on multiple imputed data. Each outcome variable at the primary end point (T_4_) will be included as the outcome variable in a linear regression, with group as the main predictor and the outcome variable at baseline (T_0_) and stratification factors included as covariates. Adjusted means in each group, as well as the adjusted mean difference, will be calculated. In the event of outliers, quantile regression will be used in place of linear regression and adjusted median differences at the primary end point (T_4_), and as exploratory analyses, the other time points will be estimated. Following recent research suggestions [65], we chose to provide randomization-based inferences; that is, statistical significance will be based on Fisher exact *P* values [66] from 100,000 permutations for the adjusted mean differences and uncertainty intervals will be based on 95% Fisher intervals. The sharp null hypothesis tested will be that being randomized to CM has an identical effect on participants’ outcomes as being randomized to CL.

Given the conceptual overlap between stratification factors and the outcome measured at baseline, only the stratification factors for anxiety and depression will be included in the linear regression assessment of the primary outcome (DERS-SF). For the linear regression assessment of depression and anxiety symptoms, only the DERS-SF stratification factor will be included. For the linear regression assessing QoL, both stratification factors will be included.

In addition to testing for group differences at the primary end point (T_4_), we will explore group differences at T_1_, T_2_, T_3_, and T_5_ on the primary and secondary outcomes. The overall sample mean at T_0_ will be presented for comparison.

The adjusted SMDs will be calculated as the adjusted group mean difference (CM–CL) divided by the residual SD estimated from the model. In the case of outliers, standardized median difference will be calculated. By using the residual adjusted for baseline outcome scores, this is effectively an effect size on the difference scores or for repeated measures [67].

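### The DERS-SF, anxiety and depression models each leave out one of the two factors used to stratify randomization, for a reason that is not statistical; the cost is small and easily avoided

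*Protocol article*

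**What the plan says.** Under Randomization and Blinding, allocation is blocked (sizes 4, 6 or 8) and stratified by two binary factors: "Randomization is stratified by baseline depressive and anxiety symptoms" (60 or more on either PROMIS scale, against below 60 on both) and DERS-SF (below 45, against 45 or more). That makes four cells.

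Under Statistical Analysis Plan, Primary Aim, the general model has group as predictor, with the baseline outcome "and stratification factors included as covariates". A later paragraph narrows this by outcome. For the primary outcome, "only the stratification factors for anxiety and depression will be included in the linear regression assessment of the primary outcome (DERS-SF". For depression and anxiety, "only the DERS-SF stratification factor will be included". QoL keeps both factors. The reason offered is that the factors and the baseline outcome overlap in concept.

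Inference is randomization-based: P values come "from 100,000 permutations for the adjusted mean differences", with 95% Fisher intervals. The text does not say whether the permutations respect the strata or blocks.

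**The concern.** A stratification factor is a baseline variable that the allocation has balanced by design. Leaving it out of the model does not bias the treatment contrast, but any outcome variance it explains stays in the residual. Resemblance between two baseline covariates is no reason to drop one: their collinearity affects their own coefficients, not the group difference, and keeping both costs about one degree of freedom.

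The reason is also applied unevenly. The Secondary Outcomes section lists depression among the domains of the QoL score, so QoL overlaps with the anxiety/depression factor too, yet its model keeps both factors.

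The choice matters slightly more here because the P values are presented as exact. A randomization test is exact when its reference set contains the allocations that the scheme could have produced. If the permutations ignore the strata, the covariates are the only route by which the stratified design enters the analysis, and three models, including the primary one, have lost one of them.

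**Working it through.** **Inputs from the article.** Two factors with two levels each and blocks of 4, 6 or 8 (Randomization and Blinding); two-sided 0.05, SMD 0.5, baseline-to-post correlation r from 0.3 to 0.6 (Power Analysis); 61 + 75 = 136 participants who completed T4 (Results).

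**Step 1. The plan's own figure.** The article says "participants (n=100) with complete data at T_4" "will provide more than 80% power to detect a medium (SMD=0.5) group difference" at r = 0.3. Reading 100 as the total, 50 per arm:
- SE = √(1 − 0.3²) × √(2/50) = 0.954 × 0.200 = 0.191
- Power = Φ(0.5/0.191 − 1.96) = Φ(0.66) = 74.6% (73.7% with the noncentral t)

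The stated 80% is not reproduced; it needs about 116 in total. This is a separate matter: the power model contains only group and baseline score, so the stratification factors play no part in it.

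**Step 2. What leaves each model.**

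| Outcome | Factor kept | Factor dropped | Information lost |
|---|---|---|---|
| DERS-SF | anxiety/depression | DERS-SF | only a jump or curvature at 45, since continuous DERS-SF stays |
| Anxiety | DERS-SF | anxiety/depression | also the only term carrying baseline depression |
| Depression | DERS-SF | anxiety/depression | also the only term carrying baseline anxiety |
| QoL | both | none | none |

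**Step 3. Precision.** If omitted baseline scores have partial correlation ρ with the T4 outcome, given the terms already in the model, including them multiplies the residual variance by 1 − ρ². The article gives no ρ, so 0.1 to 0.3 is assumed.
- ρ = 0.1: variance down 1%; 136/0.99 = 137.4, worth about 1 more completer
- ρ = 0.3: variance down 9%; 136/0.91 = 149.5, worth about 13 more completers

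This range is for the continuous scores; a binary factor recovers part of it.

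**Step 4. Permutations.** Simulation with 3000 trials per scenario, 299 permutations each, N = 136, four strata and blocked allocation. Assumed, not in the article: multivariate normal baselines correlated 0.6 to 0.7, the DERS-SF cut at the mean, the PROMIS cut at +0.8 SD, complete data, and a step effect of the dropped factor beyond the linear baseline of 0, 0.5 or 1.0 SD. Restricted permutations were drawn within strata, not within blocks. Type I error (Monte Carlo SE √(0.05 × 0.95/3000) = 0.004):

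| Model | Step | Plan's covariates, unrestricted | Both factors, within strata |
|---|---|---|---|
| DERS-SF, r = 0.3 | 0 | 0.056 | 0.054 |
| DERS-SF, r = 0.6 | 0 | 0.047 | 0.047 |
| DERS-SF, r = 0.6 | 0.5 SD | 0.046 | 0.045 |
| DERS-SF, r = 0.6 | 1.0 SD | 0.041 | 0.045 |
| Anxiety, r = 0.6 | 0 | 0.053 | 0.054 |
| Anxiety, r = 0.6 | 0.5 SD | 0.044 | 0.051 |
| Anxiety, r = 0.6 | 1.0 SD | 0.039 | 0.050 |

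**Step 5. Power at SMD 0.5, with the two changes separated.**

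| Model | Step | Plan, unrestricted | Plan, within strata | Both factors, unrestricted | Both factors, within strata |
|---|---|---|---|---|---|
| DERS-SF, r = 0.3 | 0 | 0.843 | 0.853 | 0.842 | 0.849 |
| DERS-SF, r = 0.6 | 0.5 SD | 0.944 | 0.945 | 0.950 | 0.952 |
| DERS-SF, r = 0.6 | 1.0 SD | 0.922 | 0.932 | 0.952 | 0.952 |
| Anxiety, r = 0.6 | 0.5 SD | 0.941 | 0.944 | 0.942 | 0.947 |
| Anxiety, r = 0.6 | 1.0 SD | 0.922 | 0.938 | 0.950 | 0.955 |

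At the 1.0 SD step the plan loses about 3 points of power, and restoring the covariate recovers more of it than restricting the permutations does. At 0.5 SD or less the difference is under 1 point.

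**The case against.** The best defence is that the article specifies its models clearly and loses almost nothing in the primary one. The dropped DERS-SF factor is a cut of a score already in the model, and the Sensitivity Analyses section plans generalized additive models for a nonlinear baseline relation, together with parametric P values and intervals. This stands for DERS-SF. It does not restore the other symptom scale to the anxiety and depression models.

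A reader might infer that every model drops a factor, or that the plan contradicts itself. Neither holds. QoL keeps both factors, and the later paragraph is an explicit, reasoned exception to the general covariate sentence, so an analyst knows which terms enter each model.

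A reader might also infer that the permutations are unrestricted. The article is silent on this, and a condensed article may leave the resampling scheme to the full plan or the code. This part is therefore a request to state the scheme, not an error found.

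Finally, adding further baseline scores is an optional gain in efficiency, not a correction. That is fair, and it is why the point ranks low.

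**Conclusion.** The point holds as a low-severity, nearly free improvement. Three models, including the primary one, omit a randomization factor without a statistical reason. The loss is negligible for DERS-SF unless there is a step at the cut. It is clearest for anxiety and depression, at 1% to 9% of residual variance under the assumed partial correlations.

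If the permutations ignore the strata, the P values and intervals are at most mildly conservative: type I error of 0.039 to 0.041 under a 1.0 SD step, and near nominal otherwise. For DERS-SF even that 0.041 lies within about one Monte Carlo SE of its comparator, 0.045. The check shows no inflation, and omitting a factor balanced by randomization gives no reason to expect bias.

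A stronger reading, that type I error could fall to about 2%, is not supported. A small simulation (250 trials, n = 224, SE about 1 point) did give 2.0%, but its own reference SDs were 0.103 with unrestricted and 0.100 with stratified permutation. A reference distribution 3% too wide implies 2 × [1 − Φ(1.96 × 1.03)] = 0.0435, which agrees with the larger check.

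The sizes rest on assumed correlations and step effects and on complete data; multiple imputation was not simulated.

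**What to change.** Replace the outcome-specific paragraph with one rule: both stratification factors enter every model together with the baseline outcome. Preferably add the continuous baseline DERS-SF, PROMIS anxiety and PROMIS depression scores, which Table 3 shows are collected at T0. State that the 100,000 permutations are drawn within the four randomization strata and their blocks.

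The cost is wording, code and a few degrees of freedom among 224 randomized participants: one for the restored factor, and two more if the continuous scores are added to the DERS-SF, anxiety or depression model.

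Timing is the one real constraint. The Results section reports that all follow-up data were in by April 2022, so the change should be documented before any outcome analysis. If that is no longer possible, keep the prespecified model as primary and report the fuller model beside it as a sensitivity analysis.
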